**Fig. 1 Fig1:**
[figure not shown]
Flow diagram of clinical trial’s phases

### Operator’s training

Prior to sample selection, operators will be trained to perform both techniques (restoration with HVGIC and restoration with hydroxide calcium cement associated with HVGIC). The training will be performed with theoretical classes and laboratory activities during 3 h each.

The operators will be specialists in Pediatric dentistry. It will not be possible the blinding of operators because of the evident differences between the techniques.

### Random allocation

The included teeth will be allocated in two parallels arms: Experimental group – HVGIC restoration, e Control group - restoration with calcium hydroxide cement associated with high viscosity glass ionomer cement (HVGIC). Teeth will be randomly assigned into one of groups considering the strata type of cavity – occlusal or occlusoproximal surfaces, according with the sequence obtained by an external researcher with a statistical software (MedCalc version 15.8, Ostend, Belgium). The randomization procedure will be performed per blocks of four. Table 1 displays the sample distribution in according experimental groups considering the strata.

**Table 1 Tab1:** Sample distribution in according experimental groups considering the strata

Groups Type of cavity	Experimental group	Control groups	Total
Occlusal	27	27	54
Occlusoproximal	27	27	54

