## Methods/design

### Trial design and ethical considerations

A non-inferiority randomized, controlled, double blind (participant and examiner) clinical trial with two parallels arms (1:1) will be performed. The present protocol follows the guidelines of the Standard Protocol Items: Recommendations for Interventional Trials (SPIRIT) as detailed in online Additional file 1.

It was approved by the local ethics committee from the Faculty of Dentistry of the University Ibirapuera (registration no. 1.670.059) and was recorded in the database for registration of clinical studies (Clinicaltrials.gov registration NCT02903979).

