#### Secondary outcome

##### Survival of restorations

Survival of restorations will be evaluated after 6, 12, 18 and 24 months through of new clinical examination using the criteria by Frencken et al. [14] to occlusal cavities and that proposed by Roeleveld et al. [18] for occlusal-proximal restorations. In occlusal restorations those that receive 0, 1 or 7 score will be considered as success, whilst for occlusoproximal cavities it will be considered as success only those that show 00 or 10 scores. In failures cases, it will be registered the number of surfaces involved in the caries progression and the repair of restoration will be performed.

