##### Data analysis

The efficacy of each treatment will be assessed by five main outcomes:Success rate of pulp vitality (Primary outcome) andsurvival of restorations (secondary outcome): Kaplan-Meier survival and the Long-rank test will be used to compare the success rates between the experimental and control groups. Cox regression model with a shared frailty will be performed in order to allow the evaluation of the influence of the variables in the results.Progression of deep caries lesions (secondary outcome): Qui-square test will be used to compare this outcome between the groups.Cost-efficacy (secondary outcome): Incremental cost-efficacy ratio will be calculated considering the ratio between the total cost of each treatment and the success rate after 2 years.Self-reported discomfort (secondary outcome): Poisson regression will be used to compare both groups and to asses of the influence of other variables on this outcome.

For all analyzes, the significance value will be adjusted to 5%.

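### Randomisation is stratified by cavity type, but the named between-arm tests do not use the stratum; using it is a free improvement, worth most for restoration survival

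*Protocol article*

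**What the plan says.** Under Random allocation, the unit is the tooth and the only stratification factor is cavity type: teeth are allocated "considering the strata type of cavity". On blocking: "The randomization procedure will be performed per blocks of four". Table 1 plans 27 teeth per arm in the occlusal stratum and 27 per arm in the occlusoproximal stratum, 108 in all.

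Under Data analysis, the comparison for pulp vitality (primary) and restoration survival (secondary) is: "Kaplan-Meier survival and the Long-rank test will be used to compare the success rates between the experimental and control groups". A shared-frailty Cox model follows, to look at the influence of variables that are not listed. For caries progression: "Qui-square test will be used to compare this outcome between the groups". Discomfort gets a Poisson regression with other variables, also not listed. Cavity type does not appear in that section.

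Under Survival of restorations, success depends on the stratum. Occlusal teeth succeed with a score of 0, 1 or 7, "whilst for occlusoproximal cavities it will be considered as success only those that show 00 or 10 scores". Pulp vitality and caries progression each have a single definition for both cavity types.

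**The concern.** Stratified allocation removes chance imbalance in cavity type between the arms. An unstratified test computes its variance as if that imbalance could still occur. If cavity type predicts the outcome, the variance is overstated, the test rejects less often than its nominal 5%, and precision already secured by the design goes unused.

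For restoration survival there is a second reason. A single log-rank test ranks occlusal and occlusoproximal teeth together although their events are defined by two scoring systems. A stratified test compares arms only among teeth scored the same way. That argument comes from the protocol's own scoring and does not depend on any assumed rate.

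**Working it through.** **The plan's own figure.** With control success p = 0.94, margin 0.15, one-sided alpha 0.05 and power 0.80, n per arm = 2p(1−p)(1.645 + 0.842)²/0.15² = 2 × 0.94 × 0.06 × 6.18/0.0225 ≈ 31. Dividing by 0.8 for loss and multiplying by 1.4 for clustering gives 31/0.8 × 1.4 = 54.25, which rounds to the stated 54 per group. The strata play no part in this figure, and the point does not alter it.

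**Direction and size of the variance error.** Take two equal strata with success rates a and b, the same in both arms, and mean m = (a + b)/2. The unstratified variance is proportional to m(1−m). The variance under stratified allocation is proportional to w = [a(1−a) + b(1−b)]/2. The excess is (a−b)²/4, so it is never negative and vanishes when a = b. All stratum rates below are assumptions.

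| Assumed rates a/b | w | m(1−m) | Variance ratio w/[m(1−m)] |
|---|---|---|---|
| 97/91 | 0.0555 | 0.0564 | 0.984 |
| 99/89 | 0.0539 | 0.0564 | 0.956 |
| 85/55 | 0.1875 | 0.2100 | 0.893 |
| 90/65 | 0.1588 | 0.1744 | 0.910 |
| 90/50 | 0.1700 | 0.2100 | 0.810 |

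The first two rows average 94%, the protocol's control rate.

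**Simulated log-rank tests.** From the protocol: 27 teeth per arm per stratum, visits at 6, 12, 18 and 24 months, 20% loss. Assumed: stratum rates, treatment effects, two-sided 5% and independent teeth. Each scenario used 40,000 trials, or 20,000 for those with a hazard ratio of 2, which is applied to the control rates shown. Type I error is with both arms at the control rates.

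| Outcome type | Control, occlusal/occlusoproximal | Experimental | Power, unstratified vs stratified | Type I error, unstratified vs stratified |
|---|---|---|---|---|
| Pulp vitality | 94/94 | 79/79 | 58.6% vs 58.5% | 4.5% vs 4.5% |
| Pulp vitality | 97/91 | 88/70 | 59.0% vs 60.2% | 4.5% vs 4.5% |
| Pulp vitality | 99/89 | 93/65 | 59.5% vs 62.4% | 4.2% vs 4.6% |
| Restoration survival | 85/55 | 70/35 | 42.8% vs 47.1% | 3.8% vs 4.7% |
| Restoration survival | 85/55 | hazard ratio 2 | 49% vs 55% | 3.9% vs 5.0% |
| Restoration survival | 90/65 | hazard ratio 2 | 39% vs 44% | 4.0% vs 4.9% |
| Restoration survival | 90/50 | hazard ratio 2 | 41% vs 54% | 3.0% vs 4.9% |
| Not prognostic | 80/80 | hazard ratio 2 | 41.5% vs 41.4% | not tabulated |

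The gains run from 62.4 − 59.5 = 2.9 points down to nil for pulp vitality, and from 47.1 − 42.8 = 4.3 up to 54 − 41 = 13 points for restoration survival.

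**Binary 24-month outcome, chi-square vs Cochran-Mantel-Haenszel.** At the same pulp vitality rates, power is 64.4–65.4% vs 64.6–68.7%. At 85/55 against 70/35 it is 46.6% vs 51.3%, with type I error 3.6% vs 4.9%. At 99/89 the Cochran-Mantel-Haenszel test itself runs at 5.5%, so part of its gain there is size, not precision. The protocol gives no progression rate, so these rows only illustrate.

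**Risk difference against the 15-point margin.** With equal arms averaging 94%, a simple Wald interval shows non-inferiority in 93.9% of trials unstratified vs 94.1% stratified at 94/94, 93.9% vs 94.2% at 97/91, and 94.2% vs 94.7% at 99/89. The gain is half a point at most. At a true 15-point deficit the stratified Wald version wrongly declares non-inferiority in 6.0–6.4% of trials, against 5.2–6.1% unstratified. That is a small-sample weakness of the Wald method and bears on which stratified interval to choose.

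**The case against.** The strongest reply is that this is read from silence. The section names tests without calling them unstratified, a condensed article leaves covariate lists to an analysis plan, and the Cox and Poisson models could carry cavity type. Part of this stands: nothing shows that the strata are deliberately excluded, and a reader who infers that goes beyond the text. But the article does not leave the between-arm tests open. It names the log-rank and chi-square tests for that purpose, and the Cox model sits beside the log-rank comparison without replacing it. For caries progression no model is planned at all.

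Three stronger readings are tempting and are not supported:

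- *The error bars are wrong, so conclusions could be false.* Ignoring the strata makes the named tests slightly cautious. Unstratified type I error stayed between 3.0% and 4.5% in the scenarios where it is tabulated, with no inflation. The section also specifies no confidence interval that could be called too wide.
- *The analysis pools differently defined outcomes throughout.* That is true only of restoration survival. Even there, stratified allocation balances the two scoring systems between arms, so no bias between arms follows.
- *The trial's tests are conservative overall.* This is shown only for independent teeth. The protocol expects more than one tooth per child and adds 40% for it; the named tests as described do not allow for that correlation, so their net direction of error is not established.

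It is also fair that the larger power gains rest on invented stratum rates and a hazard ratio of 2, for a secondary outcome.

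**Conclusion.** The mismatch between stratified allocation and the named tests is real, and its consequence is modest. For the primary outcome it is minor: about 0 to 3 points of log-rank power. For restoration survival it is worth correcting: about 4 to 13 points across the assumed splits, plus the different scoring criteria, which justify stratifying whatever the rates turn out to be. If cavity type is not prognostic, stratifying the log-rank test gains nothing and costs essentially nothing. All sizes assume independent teeth and stratum rates that the protocol does not give. The sample size is unaffected.

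**What to change.** State in Data analysis that cavity type enters every between-arm comparison:

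- Pulp vitality and restoration survival: a log-rank test stratified by cavity type, and cavity type as a stratum or covariate in the planned shared-frailty Cox model.
- Caries progression: a Cochran-Mantel-Haenszel test, or a model that includes cavity type, in place of the plain chi-square test.
- Discomfort: cavity type as a covariate in the planned Poisson model.
- Any non-inferiority risk difference for the primary outcome: stratified by cavity type, preferably with a score-type interval, given the Wald results above.

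The cost is wording only. Cavity type is known for every tooth at randomisation, so no new data are needed. Clustering of teeth within children needs its own handling; these changes do not supply it.

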### Sample size calculation and selection

Participants will be selected with ages ranging from 4 to 8 years searching for dental treatment, coming from the Clinic of Pediatric Dentistry of the Ibirapuera University, Sao Paulo, Brazil. The screening will be carried out under natural light with the aid of a wooden spatula. Children with potential for inclusion in the research will be referred for clinical examination. Children with at least one primary molar with deep cavitated caries lesion on the occlusal or occlusoproximal surfaces will be included.

Special needs patients using orthodontic appliance and / or systemic diseases that may influence the oral cavity, will be excluded. In addition, teeth with pulp exposure, spontaneous pain, mobility, abscess or fistula near the tooth, teeth with restorations, sealants or defects of enamel formation will be excluded.

Initial periapical radiography will also be performed to confirm the depth of the lesions as well as to exclude a possible pulpal involvement – presence of radiographically visible furca/periapical lesion - linked to clinical evaluation by PUFA index [15] - presence of ulceration, fistula and abscess, reported pain and pathological mobility. It will be considered as deep caries lesion those that will be located in the inner third of dentin.

To perform the sample size calculation, the expected success rates of pulp vitality using a calcium hydroxide cement as pulp capping material was considered 94% in 12–29 months [16]. It was considered that a clinically significant difference was 15% in the success rate between the groups. Therefore, considering a significance level of 0.05 and a power of 0.80, using a one-tailed test for non-inferiority studies, with a 20% increase due to a possible sample loss and 40% by cluster of more than one tooth per children, we reached the final rounded number of 54 teeth per group, resulting in 108 teeth in total [17].

Recruitment are taking place from November 2016 to April 2018. After allocation and treatment in one of the groups, with mean of 1 month per participant, these will be followed up for 24 months. Figure 1 displays the flow diagram of clinical trial’s phases.

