### Allocation concealment mechanism

The generated sequence will be distributed in numbered sequentially opaque sealed envelopes, which should be opened by the dental assistant immediately before of the restorative procedure, after selective caries removal.

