## Discussion

Studies focusing in smart and comfortable techniques to children’s treatment should be conducted in order to guide the dentists to use of friendly-patient approaches. Thus, this is the first clinical trial that will evaluate as primary outcome the success rate considering the pulp vitality between restoration with calcium hydroxide cement associated with HVGIC and HVGIC restoration for treatment of deep caries lesions in primary molars in according the philosophy of ART.

The evaluation of this outcome will take into account clinical signs associated with symptoms, since that the most of the previous studies considering the survival of restoration as the primary outcome and not pondering the pulp condition. However, the main reason to use the pulp capping material is to protect the pulp tissue. Thus, it should be considered in the evaluation.

Others secondary outcomes will be considered. The choice of outcome measures was based on the efficacy of the treatment, but also in patient-centered outcomes, thinking in about the practice-based evidence where the preference of patient should be englobed in the treatment choice. Analysis of cost will be also performed in order to project the incremental cost of the treatments with higher failure rate for the public health manager.

This is important to highlighted that it will not be possible the blinding of the operators because of the evident differences between the both techniques. Nevertheless, to minimize this situation, the allocation of the treatments will be only performer after the selective caries removal. Furthermore, the patient and examiner can be considered as blinded.

Thus, our study desires to answer if it is possible to restore deep caries lesion of primary teeth only with HVGIC considering the ART philosophy. Since that this hypothesis was sustained, the pediatric dentistry can be used a friendlier technique to deep caries lesion management.

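### One fixed block of four within visible strata could let someone who tracks allocations foresee up to about a third of them, which weakens the safeguard of allocating after caries removal

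*Protocol article*

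**What the plan says.** All references are to the protocol article.

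- **Trial design and ethical considerations:** a "clinical trial with two parallels arms (1:1) will be performed".
- **Random allocation:** "Teeth will be randomly assigned into one of groups considering the strata type of cavity – occlusal or occlusoproximal surfaces". The order is fixed "according with the sequence obtained by an external researcher with a statistical software", and "The randomization procedure will be performed per blocks of four". No other block size is named. Table 1 plans 27 teeth per arm in each stratum, so 54 per stratum.
- **Allocation concealment mechanism:** the sequence is held in opaque sealed envelopes in numbered order, "which should be opened by the dental assistant immediately before of the restorative procedure, after selective caries removal".
- **Operator's training:** "It will not be possible the blinding of operators because of the evident differences between the techniques".
- **Discussion:** the operators' lack of blinding is acknowledged, and "to minimize this situation, the allocation of the treatments will be only performer after the selective caries removal".

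The article does not say how many operators there are, who knows the block size, or whether any one person sees all allocations in a stratum.

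**The concern.** Late opening of the envelope protects the excavation step only if the arm is unknown while the operator excavates. With a single block size, past allocations carry information about the next one. The stratum is visible before treatment starts, all recruitment is at one clinic, and a dental assistant opens the envelopes at the chairside. A child may also contribute more than one tooth, so the same team may see successive allocations.

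Excavation is the step at stake. It comes just before allocation and acts close to the pulp, and the primary outcome is pulp vitality. The planning figures leave little room for differences in handling between arms. At the assumed 94% success, about 54 × 0.06 = 3.2 failures per arm are expected, and the 15-point difference corresponds to 54 × 0.15 = 8.1 teeth per arm.

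**Working it through.** **Inputs.** Block size 4 (Random allocation); ratio 1:1 (Trial design); 54 teeth per stratum (Table 1); 108 teeth in total (Sample size calculation and selection). Assumption: blocks run separately within each stratum, and the observer knows where each block starts.

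**The plan's own figure.** The article gives no predictability figure. The total used below can be reproduced: 2 × 0.94 × 0.06 × (1.645 + 0.842)² / 0.15² = 31.0, so 31 per group. Then 31 × 1.2 = 37.2, rounded up to 38, and 38 × 1.4 = 53.2, rounded up to 54. This agrees with "we reached the final rounded number of 54 teeth per group, resulting in 108 teeth in total".

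**Step 1: an observer who sees everything, full blocks.** A 1:1 block of four has six equally likely orders.
- Positions 1 and 2 are never certain.
- Position 3 is certain when the first two are the same arm: 2 of 6 orders, or 1/3.
- Position 4 is always certain.
- Share certain: (0 + 0 + 1/3 + 1) / 4 = 1/3.

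**Step 2: planned stratum size.** 54 = 13 × 4 + 2, and the two leftover teeth are never certain. Per stratum 13 × 4/3 = 17.3; for both strata 34.7 of 108 = 32.1%.

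**Step 3: best guess.** Success by position is 1/2, 2/3, 2/3 and 1, a mean of 17/24 = 70.8%. Over 54 teeth it is (13 × 4 × 17/24 + 1/2 + 2/3) / 54 = 70.4%, against 50% for unpredictable allocation.

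**Step 4: operators who know only their own teeth.** Assume k operators, each tooth equally likely to go to any of them, no sharing, and block size and boundaries known. Position 3 is certain with probability (1/3) × 1/k². Position 4 is certain when the same operator treated both earlier teeth of the arm that is used up, with probability 1/k². The mean over four positions is (4/3)/(4k²) = 1/(3k²).

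| Operators | Certain, by formula | Certain, by simulation |
|---|---|---|
| 1 | 33.3% | 33.3% |
| 2 | 8.3% | 8.5% |
| 3 | 3.7% | 3.7% |
| 4 | 2.1% | 2.1% |

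At the planned sizes, two such operators would be certain of 34.7 / 4 = 8.7 of 108 teeth (8.0%).

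**Step 5: varying block sizes.** Simulated for 54 teeth per stratum, sizes equally likely, with one observer who sees every allocation and knows the set of sizes but not which is drawn.

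| Block sizes | Certain | Best guess correct |
|---|---|---|
| 4 only | 32.1% | 70.4% |
| 4, 6 | 5.4% | 69.0% |
| 2, 4, 6 | 4.0% | 70.1% |
| 4, 6, 8 | 2.2% | 67.8% |

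**Step 6: balance.** Since 54 is not a multiple of four, Table 1's 27/27 requires the two leftover teeth to fall one in each arm. The probability is 4/6 = 2/3 per stratum and 4/9 for both.

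**The case against.** The strongest reply is that the one-third figure needs conditions that the article does not state: knowledge of the block size and sight of every earlier allocation in the stratum. The article speaks of operators in the plural, gives the sequence to an external researcher, and has an assistant open the envelopes. Being unblinded means only that an operator knows the technique being performed. This stands, and it makes one third an upper bound. Step 4 shows how fast the figure falls when knowledge is divided. However, an assistant who opens all the envelopes could hold the whole tally, so the upper bound cannot be excluded either.

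Second, withholding the block size is a detail that a journal article may leave to the full protocol. That also stands, so its absence here is not held against the plan. The point rests on the stated choice of one fixed size.

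Third, eligibility is settled largely by screening, clinical examination and radiograph before treatment. Caries removal is specified alike in both arms, and outcome examiners are blinded. This limits the routes to bias, and it makes selective inclusion less likely than a difference in excavation. It does not close the excavation route, because the extent of removal is a judgement made before the envelope is opened.

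A reader might infer that operators see every past allocation, that a third of allocations will in fact be known, or that the safeguard is defeated. The documents support none of these. Even in the worst case about two thirds of allocations are not certain, and late opening still gives those some protection.

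**Conclusion.** The concern holds as a weakness in the stated allocation scheme. A fixed block of four in two visible strata, with unblinded operators, makes at most about 35 of 108 allocations (32%) foreseeable with certainty. That bound assumes an observer who knows the block size and tracks all allocations in a stratum. It drops to about 8% for two operators who share nothing and split the teeth equally; that split is an assumption, since the article gives no number of operators. The safeguard in the Discussion is therefore weaker than presented, but not void.

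No bias in pulp vitality has been estimated, and its direction for the non-inferiority conclusion is unknown. The best-guess rate of about 70% should not be counted as a harm that the remedy cures, because varying the block sizes hardly changes it. The gain lies in removing certainty.

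**What to change.** **For teeth not yet allocated:** have the external researcher generate each stratum's remaining sequence with randomly varying block sizes, for example 2, 4 and 6, or 4, 6 and 8, and not disclose them to operators or assistants. Certain predictions then fall from 32% to about 4% or 2%; best-guess success stays near 68–70%.

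**Cost:** a new sequence and new envelopes for the remaining teeth, and arm sizes that may end slightly off 27/27. If the new sequence starts at the end of a block and a stratum closes at exactly 54, the worst split is 28/26 with sizes 2, 4 and 6 (an even number of teeth from an open block of six leaves a difference of at most 2). With sizes 4, 6 and 8 it is 29/25 (four teeth of one arm from an open block of eight). Blocks of four can already give 28/26.

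**If all teeth have been allocated:** the article gives April 2018 as the end of recruitment, so this may apply. Qualify the Discussion's statement by adding that the fixed block size may have allowed some allocations to be foreseen. Comparing baseline lesion features by position in the block can check for selective inclusion, but it cannot detect differences in excavation depth and should not be presented as doing so.
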